### Objectives and underlying premises of PC+

This overall study aims to evaluate the effects of cardiology PC+ centre on the Triple Aim outcomes. The underlying premises of the researchers on the effects of the intervention are that the cardiology PC+ centre will result in an (at least) equivalent health of the population, improved quality of care as experienced by patients and a reduced number of referrals to hospital-based outpatient cardiology care, and hence reduced health-care costs.

The underlying premises are grounded on several hypotheses. Firstly, it is supposed that the health of the study population (patients with non-acute and low-complexity cardiology complaints) will be at least the same, since the patients receive the same diagnostic tests and the care is provided by health-care professionals with the same level of expertise. Thus, the cardiology PC+ centre and hospital-based outpatient cardiology care will lead to the same health outcomes. After the introduction of PC+, the patients who need more specialized hospital care are likely to be referred by their GP to the hospital and the patients who do not need hospital care will remain in primary care.

Secondly, the aim of the introduction of PC+ is to improve patients’ experience of care. In this study the component patients’ experience of care is based upon the six dimensions of health-care performance of the Institute of Medicine (IOM), which partially overlaps with the last premise about health-care costs [19]. It is supposed that PC+ will improve: 1) the effectiveness of care since PC+ will result in fewer unnecessary referrals to hospital-based outpatient cardiology care, thus less overuse of care, 2) the timeliness of care since PC+ will decrease the waiting time, 3) the patient-centredness of care since an underlying rationale of PC+ is being respectful and responsive to individual patient preferences, needs and values, and 4) the efficiency of care since PC+ will result in less waste of expensive hospital-based outpatient cardiology care. Efficiency of care is related to health-care costs, therefore it will be included in this dimension. In addition, it is supposed that PC+ has no effect on the level of 5) safety of care and 6) equity of care and thus it is supposed that these will remain at the same level.

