### Sub-study 1: the quantitative study

#### Aim

The aim of the quantitative part is to measure the effects of the PC+ intervention on the population’s health, patients’ experience of care and health-care costs. To measure the effects the researchers will use the following sources: patient questionnaires, data from the cardiology PC+ centre, data from the regional hospital and health insurance claims data. The data will be collected at four different time points, namely at baseline, before the patient has the first consultation with the cardiologist (T0), a week after the first consultation (T1), 3 months after the first consultation (T2) and 6 months after the first consultation (T3). The outcome parameters, including the dimensions, outcomes, concepts, methods and time frame, are summarized in Table 1.

**Table 1 Tab1:** Overview of the outcome measurements

Dimension	Outcome measure	Concept	Method	Data collection time			
				T0	T1	T2	T3
Population’s health	Health status, health-related quality of life	EQ-5D-5 L	Questionnaires	X	X	X	
		EQ-VAS		X	X	X	
		SF-12		X		X	
Experience of care	Effectiveness	EQ-5D-5 L	Questionnaires	X	X	X	
		Number of referrals	Data^a^	X		X	X
	Timeliness	Time between referral of the GP and appointment at the PC+ centre/hospital	Questionnaires	X	X		
	Patient centred	Questions about the experiences of patients with health care	Questionnaires		X		
	Safety	% Hospital admissions	Data^a^				X
		% Emergency care visits					X
	Equity	Subgroup analysis, e.g. educational level and age	Questionnaires	X		X	
Health-care costs	Health-care costs: primary care, PC+, secondary care and diagnostics	Health insurance claims data	Data^a^				X
	Efficiency	Number of consultations	Data^a^				X
		% Hospital admissions					X
		% Patients referred to hospital after PC+					X

T0 – at baseline: before the consultation

T1 – within a week after the consultation

T2 – 3 months after the consultation (follow-up)

T3 – 6 months after the consultation (follow-up)

^a^Data of the PC+ centre, the hospital and Vektis

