#### Experience of care

The experience of care will be measured using the perspective of the patient, i.e. the patient’s interaction and experience with the health-care system. The outcome parameters are based upon the six dimensions of health-care performance of the IOM: safety, effectiveness, equity, timeliness, patient-centredness and efficiency [19]. As mentioned above, efficiency will be included in the dimension health-care costs.

Effectiveness of care will be measured with the EQ-5D-5 L questionnaire and the percentage of referrals to hospital-based outpatient cardiology care. On the one hand, effectiveness will be measured using the EQ-5D-5 L scores, where it is analysed whether the health of the population is improved after a follow-up of 3 months. On the other hand, effectiveness will be measured using the number of referrals to hospital-based outpatient cardiology care, where it is analysed whether this number is decreased in the period from 2013 to 2017.

Timeliness of care will be examined by measuring the waiting time (in days) between the day the patient is referred by his GP and the day of the first consultation with the cardiologist.

Patient-centred care will be measured using items based on the Consumer Quality (CQ) index. The CQ index is a standardized method for measuring experiences of patients with health care [38]. The questionnaire (T1) includes 30 questions about the experiences of the patients with health care, with specific regard to their experiences with the health-care professionals (e.g. *‘Did you feel welcome and at ease?’* and *‘Did the health-care professionals listen attentively?’*).

Safety of care will be measured using data that will be made available by the hospital concerning: 1) hospital admissions; 2) emergency care visits.

Equity of care will be examined by performing subgroup analysis on all outcome measures regarding educational level (high versus low) and age (lower than median and higher than median).

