#### Data analysis

To investigate the effect of PC+ on population health, patients’ experience of care and health-care costs an intention to treat analysis will be conducted. The between-group comparisons will be analysed with multilevel analysis to account for the dependency of observations in time. We will apply a two-level linear mixed model (time, participants) and the level of statistical significance will be set at 0.05 (two-tailed). Separate models (random intercept) will be set up for each outcome measure. The independent variables in each model are a dummy variable indicating the group (control group = reference category), three dummy variables for time (T0 = reference category) and the interaction variable between group and time.

To correct for the possible confounding influence of baseline characteristics of the patients (e.g. age, gender, level of education, native country and health-care costs) and the GP characteristics (e.g. age, gender and practice) a propensity score will be added into the multilevel model. The propensity score will be estimated using a logistic regression model with treatment group (control or intervention) as dependent variables and baseline variables (patient and GP characteristics) included as independent variables. Only baseline variables that are related to the outcome variable (with a *p*-value smaller than 0.10) are included in the propensity score [25].

If normality assumptions are violated, outcome variables will be log-transformed and if necessary non-parametric tests will be used.

SPSS version 22 is used to analyse the data.

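### Equity is to be judged by subgroup analysis with age cut at the sample median, and no subgroup-by-group interaction is named: the cut loses age information, and the difference in effect that equity concerns is not among the stated estimates.

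*Protocol article*

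**What the plan says.** In the protocol article, the equity paragraph under Outcome parameters, Experience of care, gives the method in one sentence: "Equity of care will be examined by performing subgroup analysis on all outcome measures regarding educational level (high versus low"), and by "age (lower than median and higher than median"). The equity row of Table 1 adds only "Subgroup analysis, e.g. educational level and age" and names no test.

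The Data analysis section lists the independent variables of each model: a group indicator, "three dummy variables for time (T0 = reference category) and the interaction variable between group and time". A propensity score is added for confounding, and "the level of statistical significance will be set at 0.05 (two-tailed"). No term crosses group with age or with education.

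The section Objectives and underlying premises of PC+ states the expectation to be examined: "it is supposed that PC+ has no effect on the level of 5) safety of care and 6) equity of care". No rule is given for concluding that this expectation has been met.

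**The concern.** Equity of effect is a question about a difference: does PC+ work differently for older and younger patients, or for more and less educated ones? A result within one subgroup does not answer it. The answer is the contrast between subgroup effects, which is the interaction, and no interaction of that kind is named.

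Two separate things are at stake.

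- **Information on age.** Splitting at the median treats everyone on one side as the same age and makes the cut depend on the sample. A real gradient in effect with age becomes harder to see.
- **Interpretation.** Without a stated contrast, a reader of the results may compare p-values across halves. One significant and one non-significant half looks like inequity even when the effects are identical. Two similar p-values do not show equality either, and unchanged equity is what the article premises. Because the method applies to all outcome measures and two factors, there would be many such comparisons.

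**Working it through.** **Inputs from the article** (Sample size and power calculation; Data analysis): p0 = 0.12, p1 = 0.06, mean p = 0.09, ratio 1, z values 1.96 and 0.84, 358 evaluable patients per group, two-sided 0.05.

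**Assumptions, not in the article:** two age halves of equal size within each group; the referral proportions stand in for the other outcomes; age is normal or uniform, shown as a range; any change of effect with age is linear.

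**1. The plan's own figure.** N = (1.96 + 0.84)² × 0.09 × 0.91 × 2 / 0.06² = 7.84 × 0.0819 × 2 / 0.0036 = 356.7. With unrounded z values it is 357.1, which rounds up to 358, so the stated figure reproduces. Power at 358 per group is 80.2%.

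**2. Information kept by a median split.** Relative efficiency is the squared correlation between age and its above/below-median indicator.
- Normal age: 2/π = 0.637, equivalent to needing 1/0.637 = 1.57 times the patients.
- Uniform age: (1/2)² / (1/3) = 0.75, equivalent to 1/0.75 = 1.33 times the patients.

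Suppose continuous age gives 80% power for the interaction, so the expected z is 1.96 + 0.84 = 2.80. After the split:
- Normal: Φ(√0.637 × 2.80 − 1.96) = Φ(0.275) ≈ 0.61.
- Uniform: Φ(√0.75 × 2.80 − 1.96) = Φ(0.466) ≈ 0.68.

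**3. Identical effect in both halves, read by within-half p-values (conditional on that reading).** Each half has 358/2 = 179 per group, and power there for 12% versus 6% is h = 0.509. Both halves are significant with probability h² = 0.26, neither with (1 − h)² = 0.24, and exactly one with 2h(1 − h) = 0.50.

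The article states power only for the referral outcome, so other values are needed. For whole-sample power P, let δ = 1.96 + z_P and h = Φ(δ/√2 − 1.96) + Φ(−δ/√2 − 1.96).

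| Whole-sample power | Power in one half | Exactly one half significant |
|---|---|---|
| no effect | 0.05 | 0.095 |
| 0.50 | 0.283 | 0.41 |
| 0.70 | 0.420 | 0.49 |
| 0.80 | 0.508 | 0.50 |
| 0.90 | 0.630 | 0.47 |
| 0.95 | 0.722 | 0.40 |
| 0.99 | 0.858 | 0.24 |

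**4. Interaction test under the same identical effect.** The false-signal rate is 5% by construction; 200,000 simulated data sets gave 5.0%.

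**5. Power of the interaction test itself.** The difference between two half-sample effects has twice the standard error of the overall effect. For an interaction as large as a main effect detectable with 80% power, the expected z is 2.80/2 = 1.40, and power is Φ(1.40 − 1.96) = Φ(−0.56) ≈ 0.29.

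Steps 2 and 5 show that keeping age continuous recovers information. Moving to an interaction test corrects the false signals of step 3 but does not restore power.

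**The case against.** A reader might infer that the article plans separate models in each half, compares their significance, and does so in place of interaction terms. The text does not say this. A subgroup analysis can be run with a subgroup-by-group term, the Data analysis section describes the main models without saying how subgroups are fitted, and a journal article may leave that detail to the full protocol or analysis plan. This objection stands, so the figures in step 3 are conditional on a reading rule that the article does not contain.

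A reader might also take 50% as the rate of false inequity in this study. That is not supported either. The 80% power belongs to the referral outcome, while equity covers all outcomes, for which no power is given. Where PC+ has no effect, as is premised for safety, discordance is 9.5%.

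The 64% figure is one end of a range, because the age distribution is not stated. It also says nothing about education, which the plan treats as two categories. That patients exactly at the median fall in neither half as worded is ordinary shorthand. Finally, equity is one of six dimensions of care and does not drive the sample size.

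The objection does not remove two points. The median split is written into the article and costs information however the subgroups are fitted. And no stated quantity estimates the difference in effect.

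**Conclusion.** The point holds in a limited form. The article fixes a median split of age and names no interaction of age or education with group. The split keeps about 64–75% of the information on a linear age gradient, taking interaction power from 80% to about 61–68%; normal to uniform age and linearity are assumptions. If subgroups were judged by their separate p-values, an identical effect would produce one significant half in about 40–50% of cases across overall power of 50–95%, falling to 24% at 99% and 9.5% with no effect, against 5% for an interaction test. These figures assume equal halves within each group.

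Under either approach, a non-significant result would not establish the unchanged equity that is premised. Only an interval for the difference shows how much inequity remains compatible with the data. The article does not show that a misleading comparison of p-values is intended, and the point should not be put that way.

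**What to change.** State that equity is judged by interactions within the planned models: group × age with age continuous, and group × education. For repeated outcomes use group × time × factor with all lower-order terms. Report each interaction estimate with its 95% confidence interval, and show the median-split results as description only.

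The cost is analytic, since age and education are already collected.
- **Extra coefficients.** A repeated-measures model with k follow-up time indicators needs the factor, group × factor, k time × factor and k group × time × factor terms, that is 2 + 2k: six for two follow-up times and eight for three. This applies to each factor.
- **Linearity.** A linear age term needs a check, for example with a spline.
- **Low power.** Interaction power remains low (about 29% for an interaction as large as a main effect detectable with 80% power), so the interval should be reported in place of a significant/non-significant verdict.

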#### Health-care costs

Health-care costs will be measured using health insurance claims data. This study will not cover all related health-care costs but will only focus on health-care costs (including patients’ compulsory deductible). Out-of-pocket payments and indirect costs made from a societal perspective (e.g. labour market, informal care) will not be included. The health-care costs per participant is measured over a period of 6 months after the consultation at the PC+ centre or the hospital-based outpatient cardiology care. This concerns data regarding health-care costs on primary care, PC+, hospital care and diagnostics.

Efficiency of care means, according to the IOM, avoiding waste, particularly waste of equipment, supplies, ideas and energy [19]. With regard to this research, it will be measured whether the number of consultations of patients, hospital admissions and referrals will decrease after the implementation of PC+, which is related to efficient use of equipment and health-care professionals and time of patients. Efficiency of care will be measured using data from the cardiology PC+ centre, the hospital and Vektis. The data will consist of the following items: 1) the average number of consultations at the hospital of a patient over a period of 6 months; 2) the average number of hospital admissions of a patient over a period of 6 months; and 3) the number and percentage of patients that are referred to hospital care after PC+.

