The practice-based study focuses on a cardiology Primary Care Plus (PC+) centre. In this pioneer site PC+ implies substitution of specialist care in the hospital setting with specialist care in the primary care setting and it is designed for patients with non-acute and low-complexity related health complaints. Since virtually all specialists are hospital-based in the Netherlands, PC+ is a new form of health care. In the cardiology PC+ centre cardiologists provide consultations in the primary care setting. During the PC+ consultation the patients receive a comprehensive screening and afterwards the cardiologist sends his recommendations for further treatment (if needed) to the GP. For example, the specialist informs the GP about whether a referral to hospital care is needed. Based on the recommendation, the GP discusses the options for further treatment with the patient. Moreover, within PC+ the GP remains clinically in charge of the patient. PC+ strengthens the gatekeeping and coordinating role of the GP by intensifying the collaboration and communication between the specialists and the GPs. The PC+ intervention aims to improve the health of the population and patients’ experience of care and to reduce the number of referrals to hospital care (as well as hospital-based outpatient specialist care) in order to reduce health-care costs growth. In this study, the PC+ intervention is compared to care-as-usual, both are described in detail in the methods section. This paper describes the design of the evaluation of the cardiology PC+ intervention, combining qualitative and quantitative methods.

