### Care-as-usual: hospital-based outpatient cardiology care

Hospital-based outpatient cardiology care is considered care-as-usual. All GPs are allowed to refer non-acute and low-complexity patients with cardiology-related complaints to the hospital-based outpatient cardiology care. These patients receive the same care as within the PC+ centre, i.e. the same diagnostic tests carried out by health-care professionals with the same level of expertise. After the tests the patient meets the cardiologist, the cardiologist explains the results and they discuss further treatment (if needed). This underlines a significant difference with the intervention: in the PC+ centre the cardiologist provides only a recommendation on further treatment and the GP discusses the options for further treatment (instead of the cardiologist), i.e. within PC+ the GP remains in charge. The flow of patients is illustrated in Fig. 1.

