#### Data of the regional hospital

Hospital data include two types of patients: 1) control group patients and 2) intervention group patients (patients who have had a consultation at the PC+ centre and are referred to the hospital afterwards). The collected data are similar to the data of the PC+ centre. The starting point of the data collection is the date of referral to the PC+ centre or the hospital-based outpatient cardiology care with a follow-up period of up to 6 months. In addition to the above-mentioned collected patient information, the following hospital data will be provided: the number of consultations, the number of hospital admissions and the number of emergency care visits of a patient over a period of 6 months. The data are extracted from the registration system of the hospital.

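### Efficiency item 1 counts the control group's index cardiology visit but not the equivalent PC+ visit, giving PC+ a built-in head start of one consultation per patient

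*Protocol article*

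**What the plan says.** Under Outcome parameters, Health-care costs, the protocol article lists three efficiency items. The first is "the average number of consultations at the hospital of a patient over a period of 6 months". The second is hospital admissions. The third is the number and percentage of PC+ patients referred on to hospital. The paragraph introducing them is broader: it asks whether patients' consultations fall after PC+ is introduced, links this to the use of equipment, professionals and patients' time, and names the PC+ centre, the hospital and Vektis as data sources. Item 1 itself gives no starting date.

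The section Data of the regional hospital supplies the count ("the following hospital data will be provided: the number of consultations") and the opening of the window: "The starting point of the data collection is the date of referral to the PC+ centre or the hospital-based outpatient cardiology care". Patients are then followed for at most half a year. Besides controls, the hospital data cover only "patients who have had a consultation at the PC+ centre and are referred to the hospital afterwards".

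On the index visits, the Background says: "In the cardiology PC+ centre cardiologists provide consultations in the primary care setting". The care-as-usual section says of controls: "These patients receive the same care as within the PC+ centre, i.e. the same diagnostic tests".

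Table 1 lists the number of consultations without a setting and places it at T3, which its footnote dates from the consultation, not the referral.

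**The concern.** By the protocol's own description the two index visits have the same content and differ in location. An item restricted to one location, over a window that includes the index visit, gives that visit full weight in one group and none in the other. Part of any difference then only records where the first visit took place, which the referral decision has already fixed.

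At stake is the reading of the result. The protocol presents the item as evidence of less waste and better use of professionals and patients' time. The PC+ visit also uses a cardiologist, diagnostic equipment and the patient's time, and item 1 ignores all of these. Propensity score adjustment cannot repair this, because the problem lies in the outcome definition and not in the comparability of patients.

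**Working it through.** The protocol states no expected value for this count, so there is no figure of its own to reproduce. The sample size rests on referral proportions and does not involve this item.

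**Inputs from the protocol**
- Counted: hospital consultations only (Health-care costs, item 1).
- Window: opens at referral, before the first consultation (Data of the regional hospital).
- Control index visit: at the hospital, so counted.
- PC+ index visit: in primary care, so not counted (Background; The intervention).

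**Assumptions**
- Each patient has one index visit, inside the window.
- All PC+ patients are in the denominator, with zero for those not referred on.
- A share f of patients needs m hospital consultations after the index visit. The protocol gives neither value.

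**Step 1: identical care in both groups**
- Item 1, control: 1 + f×m
- Item 1, PC+: f×m
- Control minus PC+: (1 + f×m) − f×m = 1
- Both sites counted: 1 + f×m in each group, difference 0
- Hospital visits after the index visit only: f×m in each group, difference 0

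| f | m | Item 1, control | Item 1, PC+ | Difference | Both sites, control | Both sites, PC+ |
|---|---|---|---|---|---|---|
| 0.1 | 1 | 1.1 | 0.1 | 1.0 | 1.1 | 1.1 |
| 0.2 | 2 | 1.4 | 0.4 | 1.0 | 1.4 | 1.4 |
| 0.3 | 1 | 1.3 | 0.3 | 1.0 | 1.3 | 1.3 |
| 0.5 | 2 | 2.0 | 1.0 | 1.0 | 2.0 | 2.0 |

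The 1.0 does not depend on f or m.

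**Step 2: care that differs**

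Let a be the mean number of hospital visits in controls after the index visit, and b the mean number of hospital visits in PC+ patients.
- Item 1, PC+ minus control: b − (1 + a) = (b − a) − 1
- Both sites, PC+ minus control: (1 + b) − (1 + a) = b − a

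Item 1 goes against PC+ only when b − a exceeds 1. When b − a lies between 0 and 1, item 1 favours PC+ although its patients have more cardiologist contacts in total.

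**Step 3: an illustration only**

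Suppose each PC+ patient who is referred on needs one extra hospital intake visit. Then b − a = f. Item 1 favours PC+ by 1 − f, while the count over both sites is higher in PC+ by f. For f from 0.1 to 0.5, the apparent advantage is 0.9 to 0.5 visits and the true excess is 0.1 to 0.5. Both f and the extra visit are assumed.

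**Step 4: the other window**

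Table 1 dates T3 from the consultation. The cost paragraph in Health-care costs also measures six months after the consultation, whereas Health insurance claims data starts costs at referral. If item 1 ran from after the consultation and left out the index visit, the difference in Step 1 would be 0. The protocol does not say that it does.

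**The case against.** The strongest reply is that fewer hospital visits are what PC+ is for. The section on objectives and underlying premises describes the efficiency gain as less waste of expensive hospital-based outpatient care, so moving the screening out of hospital is part of the intended effect. This stands: the hospital-only count is a legitimate measure of substitution. It does not make the count a measure of patients' consultations or time, which the efficiency paragraph also claims.

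A second reply is that the text is not uniform. Item 1 has no start date, Table 1 points to a window after the consultation, and both the introductory wording and the data sources are wider than the hospital. This also stands in part. However, the itemised definition is the most specific statement and says hospital. The only window given for the hospital data starts at referral, and nothing excludes the control index visit or adds the PC+ one. If something else was intended, the wording needs correcting in any case.

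Third, other outcomes offset the item. Health-care costs cover primary care, PC+, hospital care and diagnostics in both groups, so PC+ visits do enter that comparison. This limits the damage but does not mend item 1. Item 3 shows how often PC+ patients go on to hospital, but it has no control counterpart.

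A reader might infer that PC+ is certain to look more efficient, or that the item reverses the true direction. The protocol supports neither. A head start of one visit can be overcome, and the reversal needs onward-referral rates and visit counts that the protocol does not give. The groups are also not expected to be identical, since less severe patients should go to PC+.

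**Conclusion.** The concern holds for efficiency item 1 alone. Read with the referral-based window for hospital data, the item gives PC+ a head start of 1.0 consultation per patient when care is otherwise identical. This assumes one index visit per patient within the window and a denominator that includes PC+ patients never referred on. It also rests on the referral start, which the protocol states for the hospital data but does not repeat for the item. Treating the index visits alike brings the built-in difference to 0.

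The size and direction of the real difference in total contacts cannot be derived from the protocol. Admissions, costs, health, patient experience and the sample size are not affected. This is a correction to one outcome definition and is not critical to the study as a whole, but uncorrected the item should not be reported as evidence of efficiency.

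**What to change.** In Health-care costs, item 1, and in the matching row of Table 1:

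- Define the efficiency count as cardiologist consultations at the PC+ centre plus the hospital, per patient, over six months from referral in both groups. Alternatively, or in addition, count hospital consultations after the index consultation in both groups.
- Keep the hospital-only count as a separate outcome labelled substitution.
- Show item 3 beside the percentage of controls with any further hospital consultation after the index visit.
- Reconcile the window start. Data of the regional hospital and Health insurance claims data use referral; Table 1 and the cost paragraph in Health-care costs use the consultation.

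The PC+ centre and hospital registrations already hold the data, so the cost is revised wording and a different count. The efficiency figure will be less favourable to PC+ than the one the current definition would give.
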